**3.0. Hypothesis and Objectives:**

The primary objective of this proof-of-concept study is to determine the feasibility of the Lymfit intervention for future application in a larger trial. The purpose is then to determine if a personalized fitness program, with the help of a fitness tracker (Fitbit), can improve their activity levels, quality life, and well-being. This proof-of-concept study also aims to examine any potential safely-issues related to the remotely delivered exercise program.

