**4.3. Participants and Recruitment:**

***Inclusion criteria:*** 1) lymphoma patients who received initial diagnosis at the age of age 18-39, 2) approved by their hematologist as having no contra-indications to vigorous exercise, 3) receiving or has received chemotherapy with curative intent, 4) own a cellular phone that is able to download the Fitbit app and to complete the study questionnaires online, and 5) is comfortable with teleconferencing with at least one platform (Zoom or Teams).

***Exclusion criteria:*** 1) The patient has contra-indications to vigorous exercise, or 2) the patient doesn’t want to wear a fitness tracker due to various concerns as no Fitbit data would be collected.

***Number of subjects:*** This is a proof-of-concept study to determine if the implementation of the exercise program is feasible and acceptable in this patient population. A total of 20 participants will be recruited to participant in this study.

***Recruitment*:** They will be recruited by their hematologist at the JGH. The JGH treats 20-25 newly diagnosed HL and DLBCL/year, with both sexes represented ~equally.

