**4.5. Data Collection:**

Feasibility outcomes will be collected and documented throughout the study by the research coordinator. The Lymfit server will store the Fitbit metrics, questionnaires responses will be collected at baseline, and at 12 weeks.

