**4.5.1. Feasibility:**

This outcome will be assessed by 1) retention rate, 2) technical issues, and 3) safety (i.e., adverse events). In the bi-weekly meeting with the kinesiologist, participants will be instructed to report any adverse events during the intervention. Any technical and safety issues will be documented in a study log by the study coordinator and the kinesiologist.

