**5.0. Data Analysis:**

Descriptive statistics will be used to provide a summary of the basic demographic and physical characteristics of study participants. For the feasibility outcomes, the retention rate will be calculated as a percentage of the total number of those who are initially enrolled, and any technical and safety issues will be documented by the study coordinator. Physiologic metrics will be reported using descriptive statistics (i.e., frequency, percentage, mean, standard deviation). For all metrics captured by the Fitbit (i.e., light activity, MVPA, sedentary time, total sleep time, and steps taken), the daily averages will be computed from week 0 to week 12.

Missing data: Any day with a daily step count less than the pre-determined cut-off of 1000 steps/day will be excluded from the daily average over a week. A day will be included in the seven-day average only if the participant had more than 1000 steps in the day. A cut-off point for four out of seven days will also be required for that week to be considered a valid daily average. If there are less than four valid days of data for that particular week, that week of data for that participant will be omitted in the analysis. If a non-compliant participant had more than four invalid weeks out of the 12 weeks, they will be considered a lost to follow-up.

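### The protocol's only loss-to-follow-up rule is a step-count data-validity rule; used for retention, as the text implies, it can misclassify participants

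*Protocol*

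**What the plan says.** Section 3.0 sets the aim: "The primary objective of this proof-of-concept study is to determine the feasibility of the Lymfit intervention for future application in a larger trial". Section 4.5.1 names the outcomes that measure it: "This outcome will be assessed by 1) retention rate, 2) technical issues, and 3) safety (i.e., adverse events". Section 5.0 then says that "the retention rate will be calculated as a percentage of the total number of those who are initially enrolled". That fixes the denominator; no sentence defines the numerator.

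The only rule on who is lost stands in the next paragraph of section 5.0, under missing data, at the end of three steps:

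- Day: "A day will be included in the seven-day average only if the participant had more than 1000 steps in the day".
- Week: "A cut-off point for four out of seven days will also be required for that week to be considered a valid daily average".
- Participant: "If a non-compliant participant had more than four invalid weeks out of the 12 weeks, they will be considered a lost to follow-up".

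The protocol has two other contacts that would show whether someone is still in the study. Section 4.5 says that "questionnaires responses will be collected at baseline, and at 12 weeks", and sections 4.1 and 4.5.1 provide for kinesiologist meetings every two weeks. Neither enters a retention or loss rule. On sample size, section 4.3 says: "A total of 20 participants will be recruited to participant in this study".

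**The concern.** Loss to follow-up ordinally means that a person has left the study or can no longer be reached. Here the label is attached to the quantity of usable step data. The two overlap but are not the same, and they can part in both directions: a person can stay in the study with thin step data, or leave late with good step data up to that point.

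The valid-day test is also a step threshold, not a measure of wear. A participant who wears the tracker but walks little fails it in the same way as one who leaves it in a drawer. Section 4.3 admits patients who are still on chemotherapy, and section 4.4 plans for sedentary or symptomatic patients whose first goal is a higher step count, so low-step days are foreseeable.

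At stake is the reading of the first feasibility outcome, which is meant to inform the larger randomised trial. A retention figure that mixes attrition, inactivity and low wear would not tell the designers which problem they have.

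**Working it through.** The protocol states no expected retention rate and no derivation of the sample size, so there is no figure of its own to reproduce. The check applies the section 5.0 rule to daily patterns.

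**Inputs.** From section 5.0: a valid day has more than 1000 steps; a valid week has at least 4 valid days of 7; a participant is lost with more than 4, that is 5 or more, invalid weeks of 12. From section 4.3: 20 participants. The period is 12 × 7 = 84 days, taking the 12 weeks as the rule names them.

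**Pattern A, completer labelled lost.** Five weeks with 3 valid days and seven weeks with 7.
- Valid days: 5 × 3 + 7 × 7 = 15 + 49 = 64; 64/84 = 76%.
- Invalid weeks: 5. Since 5 > 4, the label is lost. Attending every meeting and completing both questionnaire sets does not change it.

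**Pattern B, late dropout not caught.** All days valid through week 8, then nothing, and no 12-week questionnaires.
- Invalid weeks: 9, 10, 11 and 12, so 4. Since 4 is not more than 4, the rule does not apply.
- The boundary lies slightly earlier. Stopping after day 53 (day 4 of week 8) leaves week 8 valid and gives 4 invalid weeks. Stopping after day 52 makes week 8 invalid and gives 5.

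**Pattern C, reversed order.** Eight weeks of 4 valid days, then nothing.
- Valid days: 8 × 4 = 32; 32/84 = 38%. Invalid weeks: 4, so not caught. Pattern A has twice as many valid days and is lost.

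**Effect on the outcome.** One person of 20 is 1/20 = 5 percentage points. For scale, two people moving the same way turn 18/20 = 90% (exact 95% CI 68% to 99%) into 16/20 = 80% (56% to 94%).

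**How likely a daily wearer is to be labelled lost.** Let p be the share of days that fail the step threshold. The protocol does not give p, so the range below is an assumption. Days are taken as independent with constant p, and everyone with 5 or more invalid weeks is taken to fall under the rule.
- P(week invalid) = P(Bin(7, p) ≥ 4) = w
- P(lost) = P(Bin(12, w) ≥ 5)

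| p (assumed) | w | P(lost) |
|---|---|---|
| 10% | 0.003 | about 1 × 10⁻¹⁰ |
| 20% | 0.033 | 0.003% |
| 25% | 0.071 | 0.09% |
| 30% | 0.126 | 1.2% |
| 40% | 0.290 | 25% |
| 50% | 0.500 | 81% |

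The result depends almost wholly on p: negligible up to about 25%, and large only from about 40%. Patterns A to C need no such assumption.

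**The case against.** Five points can be made for the plan.

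1. *The link to retention is inferred.* The rule stands under missing data, after the rules for Fitbit averages, and nothing says that retention equals enrolled minus those it catches. A statistical analysis plan, not shown here, could define the numerator. This stands, and it limits the claim to what can happen. It does not clear the text: if the rule concerns only the Fitbit analysis, lost to follow-up is the wrong label for it.

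2. *The rule is not stated to be exhaustive.* A reader might infer from pattern B that late dropouts will be counted as retained. The protocol does not say so. It says who is lost, not that everyone else is retained. What stands is that its only rule does not catch them.

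3. *The rule applies to a non-compliant participant.* The term is undefined and might spare someone who wears the tracker daily but walks little. This stands and weakens that example. It does not affect pattern B.

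4. *Large misclassification rates are not shown.* A reader might take the 25% and 81% figures as expected rates. They rest on assumed shares of low-step days. Participants are cleared for vigorous exercise (section 4.3) and the programme aims to raise step counts (section 4.4), so a constant 40% to 50% is not supported.

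5. *Nothing says questionnaires are discarded.* A reader might infer that low-wear participants lose their questionnaire data. Section 5.0 omits invalid Fitbit weeks only.

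It is also fair to say that the tracker is integral to the intervention, so requiring 8 usable weeks of 12 is a defensible engagement criterion. That supports keeping it as an adherence measure, not calling it follow-up.

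**Conclusion.** The point holds in a conditional form. The protocol's one loss-to-follow-up rule is a data-validity rule based on step counts, and no other numerator is given for the first-listed feasibility outcome. If the rule is used for retention, a completer with 76% valid days can be labelled lost, and a participant who stops everything after week 8 is not caught. Each such case is worth 5 percentage points with 20 enrolled. The errors can offset or add up, so the direction of any net bias is not known, and neither is the frequency.

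The documents do not support saying that retention is certainly misclassified. Use of the rule as the retention numerator is implied, not stated.

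The severity is should-fix. The study is a descriptive, single-arm proof of concept with no retention threshold for going on to the larger trial, and the data needed to report retention properly are collected in any case.

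**What to change.** In section 5.0, relabel the participant-level rule as not evaluable for Fitbit metrics (low tracker adherence), and report valid weeks out of 12 as a separate adherence measure.

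In sections 4.5.1 and 5.0, define retained as not withdrawn and with the 12-week questionnaires completed, divided by all enrolled. Other completion criteria are possible; what matters is that the definition is written down and does not depend on step counts.

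State that questionnaires from low-adherence participants stay in the analysis. This removes a doubt; it does not reverse a stated exclusion.

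The cost is a few sentences of text and one more line in a descriptive table, with no new data and no change to study procedures.

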**6.0. Funding**:

Funding for the Lymfit database and server, as well as the Fitbits, is provided by [name] funds raised during the 2019 and 2018 *Ride to Conquer Cancer*. Funding for the students are provided by the investigator’s private funds. Further funding will be sought in 2021.

**7.0. Risk and Inconvenience:**

There exists the remote possibility during vigorous exercise of adverse changes including, but not limited to, abnormal blood pressure, fainting, dizziness. There also exists mild risk of physical injuries related to exercising outdoors. These risks will be minimized by tailored instructions based on the patients’ baseline activity levels and preferences. The increase in activity will be gradual and only safe activities will be promoted during this project. Furthermore, patients who have baseline co-morbidities that may be at higher risk of injury would be excluded based on their hematologist’s assessment.

There is a theoretical risk of breach in confidentiality if someone is capable of hacking into the Lymfit server located at the Lady Davis Institute of the JGH. However, it is protected by firewalls such that that nobody, except for the investigators on the study, will have access to the data, by logging on with a unique username and password. Furthermore, the data and downstream analysis will only be used using codes and no patient identifiers will be used. Each participant will have a research ID, which will be the Fitbit ID (i.e. Lymfit 001). This coded data will protect the patient from having the Fitbit company use their personal data (only date of birth, height and weight will be provided). At the end of the study, the raw Fitbit data (with patient identifiers) will be kept on the server for 2 years, after which point it will be stored on a hard drive in [name] office, which will not be accessible to anyone but [name]. Coded data will be available to the other investigators.

**8.0. Benefits:**

The patients will be able to access their own data in real time on their Fitbit device and phone, which will motivate them to become more active. Furthermore, they can consent to have their own results of this study as well as the final study results, an option that is available on the consent form. This research has the potential to directly and immediately benefit patients by improving hrQOL, cardiovascular fitness and if sustained, decrease long-term risk factors for cardiovascular disease, diabetes and osteoporosis. Given the benefits of exercise in the general population and other cancer survivors, we anticipate that the Fitbit intervention will increase physical activity and fitness in lymphoma survivors and that this will translate into an improved QOL and reduce the fear of cancer recurrence.

**9.0. Compensation:**

# Participants will be provided with Fitbits pedometers, which they will keep even at the end of the project. This is to ensure that there is no infectious contamination between participants if these devices were to be re-used. Participants won’t be financially compensated for their time or transportation. All interventions will be done remotely (e.g., by zoom) to minimize social contact and risk of Covid transmission.

**10.0. Incidental Findings:**

We don’t anticipate there to be incidental findings in this project. Patients will have access to their data in real time via their Fitbit device and Fitbit App on their phone. If the study reveals extremely high levels of anxiety or depression, or if the Fitbit data reveals heart rates in the abnormal range, this information will be relayed to the treating hematologist. This disclosure is stated on the consent form. The hematologist has access to multiple health care professionals that can help with manage symptoms, including a nurse, a psychologist, a social worker, a pharmacist and a nutritionist. Furthermore, he/she could consult other physicians as needed (e.g. a cardiologist, psychiatrist…).

**11.0. Communication and publication of results:**

The results of this research will be communicated to the treating hematologists and health care workers that are involved in the care of lymphoma survivors. This will hopefully improve the outcome of future lymphoma survivors. The research will also be presented at meetings and conferences by any of the investigators on the study.

